### Outcome Measurement

As the primary outcome, the following parameters are defined: (1) HRQL determined using the SGRQ [25,33,36] at T_1_ to T_4_ and (2) exercise capacity / physical ability investigated with the 6MWT at T_1_ and T_2_ [25,37-39]. The choice of the 6MWT rather than the VO_2_max as a measure of physical ability is because of the multicentric real-life study design.

The secondary outcome parameters are: (1) fatigue, the leading symptom of sarcoidosis, investigated using the FAS at T_1_ to T_4_ [28,31,40-43]; (2) the psychological burden assessed with the HADS-D at T_1_ to T_4_ [26]; (3) HRQL assessed by the generic SF-36 health survey questionnaire at T_1_ to T_4_ [27,44-47]; (4) the compiled patients’ views of: the components of the individual rehabilitation programs and their perceived importance at T_1_; and (5) an evaluation of the program from the patients’ perspective at T_1_.

To achieve a 1-year follow-up of patients who return to their homes all over Germany after the end of the inpatient rehabilitation, after T1 validated questionnaires sent by post were chosen as the only data source. Dependent on the outcome of the study, a repeat of the objective measurements (lung function and exercise test) after 3, 6, or 12 months is planned as part of a RCT follow-up study.

### Data Management and Statistical Analysis Procedures

Data management will be carried out by the Centre for Public Healthcare and statistical analysis by the Institute for Biostatistics at the Hannover Medical School.

The questionnaires will be anonymized using a clinic identifier and a consecutive patient number and will be digitized in duplicate at the Hannover Medical School and entered in Microsoft Access. The database tables will then be virtually superposed to identify differences between entries. When discrepancies are found, the data entry will be compared with that of the original questionnaire and corrected so that an accurate master dataset used for the descriptive analysis and the calculation of effect sizes will emerge.

The main analyses will be performed on the total study population. Missing values will be reported and not replaced initially. Changes in both primary endpoints between T_0_ and T_1_ will be evaluated with a paired *t* test and a 2-sided type I error of 2.5%.

Because ProKaSaRe is an exploratory study, for all analyses except for the primary analysis, *P* values will be assessed descriptively and considered to be of importance for *P*<.05. Therefore, no adjustment for multiplicity will be performed. Descriptive evaluation of clinical characteristics will be conducted. Changes from baseline for continuous data will be compared by paired *t* tests and given with 95% confidence intervals for the mean difference. Categorical parameters will be compared for T_1_ to T_4_ by chi-square test. Duration of sick leave and results of the sociomedical status documented by the physician (T_0_, T_1_) and by the patient (T_2_, T_3_, T_4_), the evaluation of rehabilitation from the patients´ perspective (T_1_) and patient-attributed value to the components of the individual rehabilitation program will be presented exploratively. For the questionnaires, a covariate analysis will be run using participating centers and baseline values as independent variables and the change from T_1_ and T_2_ to T_0_ as dependent variables. Further multivariate analyses are planned.

All statistical analyses will be conducted using the SAS 9.3 software (SAS Institute Inc, Cary, NC, USA) to show the impact of the rehabilitation program on the patients’ lives.

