The psychological burden will be also documented at T_0_ using the Hospital Anxiety and Depression Scale (HADS-D) [26] and quality of life by the 36-item Short Form Health Survey (SF-36) and the St George’s Respiratory Questionnaire (SGRQ) [27]. The fatigue symptoms, which are often predominant in sarcoidosis, will be assessed by the Fatigue Assessment Scale (FAS) [28,29] and dyspnea will be measured using the Modified Medical Research Council Dyspnea Scale (mMRC)[30-32]. At 3, 6, and 12 months (T2, T3, and T4) after the rehabilitation program, the FAS, HADS-D, mMRC [30], SF-36, and SGRQ questionnaires will be completed again by the patients. Although the questionnaires at T_0_ and T_1_ will be submitted on site, the ones at T_2_ to T_4_ will be sent by post. The patients will be instructed to complete all questionnaires independently.

In addition, the patients’ views of the components of the individual rehabilitation programs and their perceived importance will be assessed at discharge (T_1_). Moreover, an evaluation of the program from the patients’ perspective will be included in the final questionnaire at T_4._

During the whole study, response shift will be assessed by a questionnaire comprising 5 questions illustrating the prospective hopes of the patient and the retrospective specific burden of disease on the patient.

Data collection by post at 3, 6, and 12 months after discharge from the clinics will proceed by means of standardized letters with enclosed questionnaires and stamped return envelopes. The completed questionnaires will be returned to the clinic at which the rehabilitation program was carried out. Nonresponding patients will be reminded to answer the questionnaire by an additional letter after 2 weeks. Further details and the distribution times of the questionnaires and the documentation of their components are shown in Figure 1 and Table 1.

**Table 1 table1:** Components of the questionnaires given at the beginning of rehabilitation (T_0_), at the end of rehabilitation (T_1_), and at 3, 6, and 12 months after the end of rehabilitation (T_2_, T_3_, and T_4_).

Component	Content
1. Core data	Age, sex
2. Diagnoses	How they were secured or their positive proof
3. Organ involvement and general symptoms	
4. Lung function tests	VC, RV, TLC, FEV_1_, sRaw, Tiffeneau-Index (each before/after bronchospasmolysis), P0.1, and Pimax (T_0_, T_1_)
5. Gas exchange	Resting and exercise blood gas analysis (25/50 Watt), Tlco SB, Tlco/VA, (T_0_, T_1_)

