### Sample Size Calculation and Statistics

Sample size calculation was carried out separately for both primary endpoints. Because both endpoints are equally important, the type I error was adjusted by Bonferroni multiplicity adjustment.

The minimal clinical difference for the health-related SGRQ corresponds to a change of 4 points in the score for patients with COPD. This value was also used in the planning of this study because no sarcoidosis-specific reference values were available. According to Jones [33], a 4-point difference between baseline values and follow-up data would indicate clinically relevant (long-term) effects. From the 95% confidence interval he observed in 97 patients, we estimated a standard deviation of 12.1. Assuming a 2-sided type I error of 2.5% and a power of 90%, the overall sample size required based on a paired *t* test would be 115 patients.

One estimated minimal clinical difference for the 6MWT distance corresponds to 26 m [34]. In absence of sarcoidosis-specific references, we suggest according to Marcon [35], a 6MWT distance of approximately 600 m (SD 80). Assuming a 2-sided type I error of 2.5% and a power of 90%, the overall sample size on the basis of a paired *t* test is 121. Thus, at least 121 patients are needed to test for both primary endpoints. To avoid a systematic “center bias,” each center should recruit at least 30 patients. Sample size calculations were performed using nQuery Advisor7.0.

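### The 3- to 12-month questionnaire results rest on separate paired t tests of whoever returned each postal form, and the adjusted model stops at 3 months

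*Protocol article*

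**What the plan says.** The Introduction names the course of health-related quality of life over the 12 months after rehabilitation as one of its main questions. Outcome Measurement lists the SGRQ at T1 to T4 as a primary outcome, and FAS, HADS-D and SF-36 at the same times as secondary outcomes. It also states that after T1 postal questionnaires are the sole source of data. Data Collection and Compilation provides one follow-up letter: "Nonresponding patients will be reminded to answer the questionnaire by an additional letter after 2 weeks".

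Data Management and Statistical Analysis Procedures then sets the analysis:

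- Population and missing values: "The main analyses will be performed on the total study population. Missing values will be reported and not replaced initially".
- Confirmatory test: the T0–T1 change in each primary endpoint, by paired t test at two-sided 2.5%. All other P values are descriptive, with .05 as the mark.
- Continuous outcomes in general: "Changes from baseline for continuous data will be compared by paired" t tests, with 95% confidence intervals.
- Covariate model: for the questionnaires only, with center and baseline value as independent variables and "the change from T_1_ and T_2_ to T_0_ as dependent variables".
- A closing remark announces further multivariate analyses without naming a method, outcome or time point.

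**The concern.** A paired t test uses only patients with both values. Without replacement, the T2, T3 and T4 tests each use whoever returned that form, and the three sets need not coincide. Each test still compares patients with their own baseline. The difficulty lies in reading the estimates as a course over time, which is what the study question asks for.

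If patients who did well reply more often, the sustained benefit is overstated. If return falls over time, the changing mix of responders can produce a trend or hide one. The T4 estimate also makes no use of the T1–T3 values of patients who did not return T4, although those values say something about how they were doing. The one specified model with center and baseline ends at 3 months, so nothing specified supports the 6- and 12-month results beyond the unadjusted responder tests.

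The Discussion intends long-term effectiveness as evidence for the health care system and for guidelines, so the 12-month estimate will carry weight even though its P value is descriptive.

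**Working it through.** **Inputs from Sample Size Calculation and Statistics.** The SGRQ threshold "corresponds to a change of 4 points in the score for patients with COPD"; for variability, "we estimated a standard deviation of 12.1"; two-sided type I error 2.5% and power 90%; at least 121 patients overall; at least 30 per center, with 6 centers.

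**The plan's own figure.** Normal approximation for the SGRQ: n = [SD × (z₀.₉₈₇₅ + z₀.₉₀) / δ]² = [12.1 × (2.241 + 1.282) / 4]² ≈ 113.6, so 114. With the noncentral t distribution n is 117, and power at the stated 115 is 89.7%. The stated 115 is reproduced to within 2 patients. There is no arithmetic error here.

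**Bias of a responder-only mean.** Let q be the share not returning T4, R the mean change in responders and N the mean change in non-responders. The mean in all patients is (1 − q)R + qN, so

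bias = R − [(1 − q)R + qN] = q × (R − N).

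The article gives neither q nor R − N, so both are assumptions. A positive gap means responders improved more.

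| Gap R − N (assumed) | q = 20% | q = 40% |
|---|---|---|
| 5 points | 1.0 | 2.0 |
| 2.5 points | 0.5 | 1.0 |
| 0 | 0 | 0 |
| −5 points | −1.0 | −2.0 |

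Against the 4-point threshold, 1.0/4 = 25% and 2.0/4 = 50%.

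**Effect on the trajectory.** Keep the 5-point gap and let non-return rise from 10% at T2 to 40% at T4. The bias goes from 0.5 to 2.0 points, a drift of 1.5 points with no change in any patient. Likewise, a true mean improvement of 4 points at T1 and 2 points at T4 would appear among 60% responders as 2 + 2 = 4 points at T4, that is, as full maintenance.

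**What a model that uses the earlier data can repair.** Simulation with assumed inputs: SD of change 12.1 at T1 and T4; correlation between the two changes 0.5–0.7; odds of return multiplied by 1.5–3 per SD of better change. The model-based estimate regresses the T4 change on the T1 change in responders and predicts it for everyone. Sizes of bias, all towards too much benefit:

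| Return at T4 | Return depends on | Responder-only bias (points) | Bias left with T1 data used |
|---|---|---|---|
| 80% | T1 change | 0.5–1.6 | under 0.1 |
| 80% | T4 change itself | 1.0–2.3 | 0.5–1.8 |
| 60% | T1 change | 1.0–3.0 | under 0.1 |
| 60% | T4 change itself | 1.9–4.3 | 1.0–3.4 |

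Using the earlier data removes nearly all of the first kind of bias and about a fifth to a half of the second.

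**Power.** The T4 tests are read at the descriptive 5% level. For a 4-point change with SD 12.1, power is 95% with 121 pairs, 89% with 96 (80% return), 85% with 84 (70%) and 79% with 72 (60%). If every center reached 30 patients, 6 × 30 = 180, and 70% return would leave 126 pairs with about 96% power.

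**The case against.** The strongest reply is that this is a condensed article of a declared exploratory study. The wording says missing values are not replaced initially, which suggests a later step, and further multivariate analyses are announced. Imputation, repeated-measures models and sensitivity analyses commonly sit in a separate analysis plan that is not shown. The statement about the total study population directly precedes the T0–T1 test and may simply mean all enrolled patients rather than subgroups.

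Much of this stands. It would be too strong to say that missing values are definitively left out, and the population wording carries little weight. What remains is what the article does fix: paired t tests for continuous changes, and a covariate model with explicit time points that ends at T2 although the listed outcome runs to T4. The two open remarks name no method and no time point, so they do not change that.

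A reader might infer four stronger points that the article does not support:

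- **That the primary test is compromised.** It is not. T0 and T1 questionnaires are handed in on site, so postal non-return cannot affect it.
- **That the 12-month test is badly underpowered.** This follows only if the 2.5% level, reserved for T0–T1, is applied to T4. At the 5% level the loss is moderate.
- **That data from patients who stop replying are discarded.** Their T1–T3 values enter the tests at those times; they are only not used for T4.
- **That the covariate model's omission of the 6MWT weakens the 12-month result.** Under postal-only follow-up there is no 6MWT after T1, and center adjustment barely moves a single-arm mean change.

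**Conclusion.** The point holds for the T2–T4 questionnaire analyses and not beyond them. The named method cannot separate a change in patients from a change in who replies, and the adjusted model stops nine months before the end of the follow-up that the study question covers. It is worth changing, but it does not threaten the confirmatory result.

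The size depends on assumptions, because the article gives no return rate and no information on how non-responders differ. With 20–40% non-return and a 5-point gap, the T4 SGRQ bias is 1–2 points, or 25–50% of the 4-point threshold. With a smaller gap it shrinks, with no gap it vanishes, and if patients who did poorly reply more often it reverses. Bias, rather than power, is the reason to act.

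Outcome Measurement also lists the 6MWT at T2 while restricting follow-up after T1 to postal questionnaires. That is a separate contradiction, and the two statements must be reconciled.

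**What to change.** Analyse SGRQ, FAS, HADS-D and SF-36 each with one mixed model for repeated measures on all observed values from T0 to T4, with time and center as fixed effects. Report the mean change from T0 at T1, T2, T3 and T4 with 95% confidence intervals.

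Add a sensitivity analysis for informative non-response, for example one in which non-responders keep their T0 value. Report the number of returned forms at each time point and compare T0 and T1 values of responders and non-responders. Replace the open word about initial handling of missing values by this defined step.

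Keep the paired t tests at T2–T4 as supportive, labelled as responder analyses with their own n. The T0–T1 confirmatory test stays as it is.

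The cost is a little more programming in SAS, which is already planned; no new data are needed. The downside is that the model relies on data being missing at random. If return depends on the T4 outcome itself, only part of the bias is removed, which is why the sensitivity analysis belongs with it.

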Rehabilitation in Germany is a statutorily regulated part of the health care system and is only approved when social participation and inclusion, daily life, and the professional activities of the patient are restricted by illness. Access to inpatient rehabilitation is only possible following a thorough investigation by physicians specializing in social medicine. Proof that all outpatient treatment options have been exhausted must also be provided.

ProKaSaRe (Prospektive Katamnesestudie Sarkoidose in der pneumologischen Rehabilitation) [Prospective Catamnesis Study of Sarcoidosis in Pulmonary Rehabilitation] is a “real-life” cohort trial and a prospective multicentric follow-up (catamnesis) study of sarcoidosis in pneumological rehabilitation. It is designed to assess the impact of a multimodal 3-week inpatient pulmonary rehabilitation on symptoms, exercise capacity, and health-related quality of life (HRQL) for adult patients with chronic sarcoidosis. ProKaSaRe has a 1-year follow-up time.

We intend to rule out seasonal influences by including patients over a recruitment phase of 12 months. By assessing changes over a long period in this cohort of chronic sarcoidosis patients, so far the largest worldwide, we hope to gain reliable insights into and sound evidence of objective and/or subjective short- and long-term health changes caused by pulmonary rehabilitation. The most important questions that should be answered with the ProKaSaRe study are:

What are the characteristics of patients treated in inpatient pulmonary rehabilitation?What are the short- and the long-term findings in view of symptoms, exercise capacity, and HRQL?Will the HRQL change after the patients are discharged and how will the HRQL develop in the 12 months following rehabilitation?

The aim of the ProKaSaRe study is to create a solid basis of empirical real-life data on the effectiveness of pulmonary rehabilitation for patients with chronic sarcoidosis, including clinical parameters, exercise capacity, quality of life, and psychological burden via a prospective, multicentric, real-life observational study.

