The inpatient rehabilitation that will be assessed consists of a clearly defined set of components developed and approved by experts in the field accredited by the German health system following assessment of their professional development and experience as heads of specialized centers. The detailed agreed-upon choice of components and the broad assessment of HRQL reflecting the subsequent patients’ reaction to their chosen and advised measures represent the strengths of ProKaSaRe.

Scientists and physicians tend to define therapeutic success by only the improvement in pulmonary function, whereas patients equate successful treatment with tangible effects in their daily lives and an improved sense of well-being. This latter ultimately determines long-lasting positive effects, as stated by the ICF [50]. For this reason, both measurements (clinical data and patients’ self-evaluation) are necessary to form a balanced picture of pulmonary rehabilitation outcomes.

Although ProKaSaRe could contain some bias because it assesses only the sarcoidosis population willing to undergo pulmonary rehabilitation and is not a RCT, it is nevertheless a real-life study. Therefore, it is likely that the results generated in ProKaSaRe will be highly generalizable.

In contrast to studies focusing on single nonpharmaceutical components of rehabilitation programs, ProKaSaRe considers the entirety of the pulmonary rehabilitation program. The participants represent a real-life sample of sarcoidosis patients rather than a selected subpopulation thereby adding to the importance of the findings for medical and economical deliberations.

If the results of ProKaSaRe show effectiveness of the rehabilitation over a long period of time, rehabilitation as documented by the study would offer perspective and justified hope to concerned patients and their families and also evidence to stakeholders in the health care system. The documented efficacy of pulmonary rehabilitation for sarcoidosis patients will fill a gap in the reference literature used to develop guidelines and efficient long-lasting treatment procedures. It may establish rehabilitation as an irreplaceable and necessary additional therapeutic option for sarcoidosis, with highly relevant outcomes, which is only effective in its entirety and is more than the sum of single administrated components.

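### The only alpha-controlled SGRQ test ends at discharge from the clinic, so it cannot separate a benefit that carries into daily life from relief during the inpatient stay

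*Protocol article*

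**What the plan says.** All places are in the Protocol article.

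- **The confirmatory test** (Data Management and Statistical Analysis Procedures): "Changes in both primary endpoints between T_0_ and T_1_ will be evaluated with a paired" *t* test, two-sided 2.5%. The same section treats all other P values as descriptive at P<.05 without multiplicity adjustment. These include paired tests of other changes from baseline and a covariate analysis of the T0-T1 and T0-T2 changes in the questionnaires. It says the analyses should show the programme's impact on patients' lives.
- **Timing and setting** (Data Collection and Compilation; Intervention): T0 is at admission, T1 at discharge, with a 3-week inpatient programme between them. "Although the questionnaires at T_0_ and T_1_ will be submitted on site, the ones at T_2_ to T_4_ will be sent by post".
- **Endpoint definition** (Outcome Measurement): the SGRQ is a primary outcome at T1 to T4.
- **Target difference** (Sample Size Calculation and Statistics): "a 4-point difference between baseline values and follow-up data would indicate clinically relevant (long-term) effects".
- **Study question** (Introduction): "Will the HRQL change after the patients are discharged and how will the HRQL develop in the 12 months following rehabilitation".
- **What patients value** (Discussion): the article contrasts the view of scientists and physicians with that of patients, "whereas patients equate successful treatment with tangible effects in their daily lives and an improved sense of well-being". It then says that both clinical data and self-evaluation are needed.

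**The concern.** Between T0 and T1 two things change together: patients receive the programme, and they live in a clinic for three weeks instead of in their usual surroundings. A one-group before-after comparison cannot separate the two. T1 is also the only post-baseline SGRQ completed before patients return home, yet it carries the only error-controlled conclusion on quality of life. The endpoint definition, the rationale for the 4 points and the stated aim all look beyond discharge.

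The course after discharge has a related difficulty. The step from T1 to T2 contains the return home and the switch from on-site to postal completion, so a worsening there cannot be read simply as loss of benefit.

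At stake is the meaning of the headline result. A significant T0-T1 change could be reported as a gain in daily life when it may partly or wholly reflect the stay. This would remain true with complete follow-up.

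**Working it through.** **1. Inputs.** From Sample Size Calculation and Statistics: SGRQ difference 4 points ("a 4-point difference between baseline values and follow-up data would indicate clinically relevant (long-term) effects"); SD 12.1 ("From the 95% confidence interval he observed in 97 patients, we estimated a standard deviation of 12.1"); two-sided alpha 2.5% and power 90% ("Assuming a 2-sided type I error of 2.5% and a power of 90%, the overall sample size required based on a paired" *t* test); 6MWT difference 26 m ("One estimated minimal clinical difference for the 6MWT distance corresponds to 26 m") with SD 80; overall minimum N = 121.

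**2. The plan's own figures.** Normal approximation, n = (SD × (z₀.₉₈₇₅ + z₀.₉₀) / difference)², with z values 2.241 and 1.282:

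- SGRQ: (12.1 × 3.523 / 4)² = 113.6, so 114; exact noncentral *t* gives 117; stated 115.
- 6MWT: (80 × 3.523 / 26)² = 117.5, so 118; exact 121; stated 121.

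The stated numbers reproduce within rounding and method (exact power is 89.7% for the SGRQ at 115 and 90.3% for the 6MWT at 121). The issue is which contrast is tested, not the arithmetic.

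**3. Smallest significant change.** With N = 121, t₀.₉₈₇₅ on 120 df is 2.270. Critical mean change = 2.270 × 12.1 / √121 = 2.50 points.

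**4. Illustration with assumed setting shifts.** Suppose the programme itself has no effect and the stay alone moves the mean SGRQ by b points. The noncentrality is b × √121 / 12.1 = 0.909 × b.

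| Assumed shift b (points) | Probability that T0-T1 is significant at 2.5% |
|---|---|
| 0 | 2.5% |
| 1 | 9.1% |
| 2 | 32.9% |
| 3 | 67.6% |
| 4 | 91.3% |

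The documents give no size for b. The table is the power curve of the planned test read at assumed shifts; it shows sensitivity and is no evidence that such a shift exists.

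**5. Power of a T0-T2 test.** The documents give no postal return rate, so 80% and 90% of 121 are assumed (97 and 109 pairs), with SD 12.1 also assumed at T2. For 4 points at two-sided 2.5%:

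- 97 pairs: 83.4%
- 109 pairs: 87.9%

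In a fixed sequence both tests must succeed. With T0-T1 power of 91.3% at N = 121 and a 4-point change at both times, joint power is at least 0.913 + 0.834 − 1 = 0.747 and at most 0.834 at 80% return. At 90% return the bounds are 0.913 + 0.879 − 1 = 0.792 and 0.879. The exact value depends on the correlation between the two changes, which is not given.

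**The case against.** **T0 and T1 may not represent home and clinic cleanly.** A reader might infer that T0 can describe only life at home and T1 only life in the clinic. The documents do not support that. No SGRQ recall period is given; a window longer than three weeks would make T1 overlap the time before admission. Under Selection of Study Centers and Participants, some patients are referred after acute hospital treatment. This stands, and it makes the home-versus-clinic contrast an inference. It does not make T0-T1 a better measure of daily life.

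**The stay is part of the treatment.** The study evaluates an inpatient programme as a whole, so relief during the stay may count as part of the package. This is a fair reading, and it supports a statement about status at discharge. It does not support one about daily life afterwards.

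**The later data are already analysed, in a self-declared exploratory pilot.** True: T0-T2 and later changes are planned, and the Discussion admits possible bias because the study is not randomised. What remains open is that no SGRQ after the return home has confirmatory status, and the change of setting is not mentioned.

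**No T1-T2 test is specified.** Also true. That part concerns only how the post-discharge course is read.

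**T0-T2 has its own mode change.** T0 is completed on site and T2 by post. This stands and must be disclosed with the result.

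**The Discussion sentence on daily life.** A reader might take it as the study's formal criterion of success. It reports the patients' view, and the article then asks for both kinds of measure.

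**Conclusion.** The point holds in a limited form. The sole alpha-controlled SGRQ test answers whether scores differ at discharge. It cannot show whether a change persists once patients are home, which is what the T1-to-T4 endpoint, the long-term rationale for 4 points and the stated aim call for.

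The size of any setting effect is unknown. Under the plan's SD and N = 121, about 2.5 points is enough for significance, so assumed shifts of 1 to 4 points would give significant results in about 9% to 91% of studies with no programme effect.

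A stronger reading would be that the T0-T1 result is invalid, or that T0-T2 would establish a rehabilitation effect. Neither follows. T0-T1 is a legitimate discharge comparison. T0-T2 remains uncontrolled and is still open to regression to the mean, natural course and selective return of questionnaires. What is warranted is a low-cost improvement in the status and wording of the contrasts.

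**What to change.** Amend Data Management and Statistical Analysis Procedures as follows:

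1. Keep the T0-T1 test at two-sided 2.5% and report its SGRQ result as change at discharge.
2. Add the SGRQ change from T0 to T2, the first measurement after the return home, as the second step of a fixed sequence: test it at the same 2.5% only if T0-T1 is significant. Claim a quality-of-life change that persists in daily life only if both are significant, and avoid causal wording because there is no control group.
3. Describe the post-discharge course also from T2 to T4, where all questionnaires are postal and follow the return home. State that T1-T2 and T0-T2 both include the change from on-site to postal completion, and that T1-T2 also includes the return home.

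**Cost.** The change needs no new data, no additional patients and no extra alpha, since the sequence uses the SGRQ's existing 2.5%. The downside is that the claim of persistence is harder to reach than the discharge result, because postal non-response lowers power. The protocol should state the return rate it expects, so that this loss is visible in advance.
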